### Intervention procedures

The SpasT-SCI-T trial outlines specific intervention procedures for each participant group. These interventions encompass blood sampling, imaging, and clinical assessments aimed at investigating sodium channel fragments as potential biomarkers and correlating their dynamics with clinical outcomes. All procedures are rigorously standardized to ensure reproducibility and protocol adherence.

#### Group 1: Healthy subjects.

Healthy participants are selected from a pre-screened volunteer registry. Upon enrollment, they are invited to the Clinical Investigation Center at Hôpital Nord at their convenience. During the inclusion visit a single venous blood sample of 4 mL is collected in BP100 tubes containing protease inhibitors to prevent biomarker degradation. The sample is processed within 2 hours of collection by centrifugation at 1500g to extract plasma, which is then stored at -80°C until analysis at the BioMINT platform. No follow-up visits or additional interventions are required for this group, ensuring minimal participant burden.

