### Participants

The selection of participants is based on strict inclusion and exclusion criteria (Table 1).

**Table 1 pone.0319635.t001:** Inclusion and exclusion criteria for study participants.

Criteria	Group 1: Healthy Controls	Group 2: SCI Patients	Group 3: TBI Patients
**Age (years)**	18–75	18–75	18–75
**Type of Trauma**	None	Acute spinal cord injury (C4–T12), confirmed by CT/MRI	Acute traumatic brain injury (Marshall Grade II or higher), confirmed by CT
**Neurological Assessment**	None	ASIA Impairment Scale (grades A to D)	Glasgow Coma Scale (GCS ≤ 13)
**Inclusion Timeline**	–	≤6 hours post-trauma	≤6 hours post-trauma
**Associated Conditions**	-See Exclusion Criteria	No concomitant TBI	No concomitant SCI
**Social Security Affiliation**	Required	Required	Required
**Exclusion Criteria**	- Minor, Pregnancy or breastfeeding. - Pre-existing neurological disorders (e.g., multiple sclerosis, Parkinson’s disease), cardiovascular or pulmonary diseases. - Psychiatric illnesses or neurodegenerative conditions- Severe trauma (e.g., multi-organ failure) - Inability to provide consent and absence of a legally authorized representative	-Same as Group 1	-Same as Group 1

SCI, spinal cord injury; GCS, glasgow coma scale; TBI, traumatic brain injury; ASIA, American Spinal Injury Association.

Inclusion Criteria:

Group 1 (Healthy Controls):

Adults (male or female) aged 18–75 years.No history of central or peripheral nervous system trauma.Absence of any chronic neurological, psychiatric, or systemic diseases.Ability to provide informed consent prior to inclusion.Affiliation with a social security system.

Group 2 (SCI Patients):

Adults (male or female) aged 18–75 yearsConfirmed acute SCI (C4-T12) based on imaging (CT and MRI).Neurological assessment using the American Spinal Injury Association Impairment Scale (ASIA): grades A to D.Inclusion must occur within 6 hours post-trauma.No concurrent TBI.Affiliation with a social security system.

Group 3 (TBI Patients):

Adults (male or female) aged 18–75 yearsConfirmed acute TBI based on CT imaging (Marshall Grade II or higher).Neurological assessment using the Glasgow Coma Scale (GCS) ≤13.Inclusion must occur within 6 hours post-trauma.No concurrent SCI.Affiliation with a social security system.

Exclusion Criteria (All Groups):

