### Justification of sample size

The study includes a total of 40 participants distributed as follows: 20 patients with spinal cord injury (SCI), 10 patients with traumatic brain injury (TBI), and 10 healthy controls. The selection of 20 SCI patients is based on the annual admission rates for SCI at the study institution, ensuring a representative sample of the population served. The inclusion of 10 TBI patients is justified to account for potential confounding factors arising from the overlapping but distinct injury mechanisms of SCI and TBI. Furthermore, 10 healthy controls are included to provide a robust baseline for sodium channel fragment levels, facilitating a balanced comparison across the three groups.

This sample size is sufficient to detect meaningful trends and associations between sodium channel fragments and clinical outcomes, including spasticity, while maintaining feasibility within the scope of a pilot study. The findings will generate preliminary evidence regarding the diagnostic and prognostic utility of sodium channel fragments in neurological injuries and will guide the design of larger-scale clinical trials.

Given the exploratory nature of this study, no formal interim analyses are planned. As the trial involves minimal-risk procedures, such as blood sampling, no pre-specified stopping rules have been established. In the event of significant deviations from the protocol or unforeseen safety concerns, the trial steering committee will consult the Ethics Committee to determine whether adjustments or study termination are necessary. All such decisions will be transparently documented and communicated to relevant stakeholders, including regulatory authorities, to ensure compliance with ethical standards.

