### Statistical methods

The primary objective of this study is to quantify sodium channel fragments in blood samples and compare their levels across the three participant groups: healthy controls (Group 1), SCI patients (Group 2) and TBI patients (Group 3). To address this objective, statistical analyses will begin with group comparisons.

1**Group Comparisons:** For normally distributed data, one-way analysis of variance (ANOVA) will be employed to identify differences in sodium channel fragment levels among the three groups. If data are not normally distributed, the Kruskal-Wallis test will be applied as a non-parametric alternative. Post-hoc analyses will follow these tests to assess pairwise comparisons, using Tukey’s test for ANOVA or the Mann-Whitney U test for non-parametric data.2**Effect Size Calculation:** Effect sizes (e.g. Cohen’s d for t-tests or η² for ANOVA) will be calculated to quantify the magnitude of differences between groups.

For secondary outcomes, analyses will focus on the temporal kinetics of sodium channel fragments and their correlation with clinical outcomes.

1**Temporal Kinetics:** Changes in fragment levels over time, measured at baseline (6 hours), during the acute phase (Days 1, 3, 5, 7), and at follow-up (Months 3 and 6), will be analyzed using repeated-measures ANOVA for normally distributed data. For non-normally distributed data, the Friedman test will be used. Bonferroni corrections will be applied during multiple comparisons.2**Spasticity Correlation:** The relationship between sodium channel fragment levels and spasticity severity in SCI patients will be assessed using Spearman’s rank correlation coefficients, with spasticity evaluated at Months 3 and 6 using the Modified Ashworth Scale (MAS).3**Subgroup Analysis (SCI Severity):** Subgroup analyses will investigate whether sodium channel fragment levels differ by injury severity. In SCI patients, severity will be categorized based on the American Spinal Injury Association (ASIA) Impairment Scale grades (A–D). Similarly, spasticity onset will be analyzed as a binary outcome (presence vs. absence). For TBI patients, the Glasgow Coma Scale (GCS) will be used to classify injury severity, enabling comparisons of sodium channel fragment levels across defined severity subgroups.

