Additional statistical methods will include multivariable linear regression models to adjust for potential confounders, including age, sex, injury severity (ASIA grades A–D for SCI, GCS scores for TBI), and concurrent medications (antispasmodics, analgesics, antiepileptics) as primary factors, as well as additional variables from Table 3 such as comorbidities (diabetes, organ failure), trauma context (type of accident), and biological parameters (hemoglobin, renal clearance) where statistically significant or clinically relevant, informed by prior literature [14,21]. This ensures that observed associations between sodium channel fragment levels and outcomes such as spasticity are robust and not influenced by baseline characteristics. Receiver operating characteristic (ROC) curves will be generated to identify threshold levels of sodium channel fragments that differentiate SCI from TBI or predict spasticity onset. To address missing data, multiple imputation methods will be applied, minimizing bias and preserving the validity of the analyses.

Continuous variables will be expressed as means with standard deviations for normally distributed data or medians with interquartile ranges for non-normally distributed data. Categorical variables will be summarized as frequencies and percentages. For all primary and secondary analyses, a two-tailed p-value < 0.05 will be considered statistically significant. Patients who die before the 3-month follow-up will be excluded from spasticity-related analyses due to insufficient time for spasticity development, but all data collected up to the time of death will be included in secondary analyses, such as demographic characterization and early biomarker levels.

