#### Baseline data.

Baseline data were systematically collected to characterize the study population and ensure comparability across the three participant groups (healthy controls, SCI patients, and TBI patients). Key baseline variables are presented in a detailed summary table to promote transparency and support balanced comparisons between groups.

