### Strengths and limitations

This study uniquely explores sodium channel fragments, providing an innovative and specific biomarker linked directly to calpain-mediated pathophysiology common to SCI and TBI. Unlike previous biomarkers, sodium channel fragments offer neuronal specificity, sustained temporal expression suitable for both acute and chronic phases, and potential for wide applicability in traumatic CNS conditions. Despite their promise, challenges remain before clinical adoption. Patient factors like demographics and comorbidities may affect fragment levels, requiring larger studies to define normative ranges and thresholds. Standardized sample processing is also essential for reproducibility. Integrating biomarker analysis into clinical workflows demands infrastructure and validation efforts.

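### Healthy controls are not matched on age or sex, the three-group test is unadjusted, and the planned regression does not clearly cover the patient-control contrast

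*Protocol article*

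**What the plan says.** Control selection is described in Group 1: Healthy subjects: "Healthy participants are selected from a pre-screened volunteer registry". Under Participants, the demographic limit is the same for every group, "Adults (male or female) aged 18–75 years". Neither section mentions matching. The group sizes are "20 patients with spinal cord injury (SCI), 10 patients with traumatic brain injury (TBI), and 10 healthy controls".

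Statistical methods treats the comparison of fragment levels across the three groups as part of the primary objective (Study aims lists the comparison with controls as a secondary objective). The method is fixed: "one-way analysis of variance (ANOVA) will be employed to identify differences in sodium channel fragment levels among the three groups", and for non-normal data "the Kruskal-Wallis test will be applied as a non-parametric alternative". Tukey or Mann-Whitney tests follow for the pairs. None of these takes a covariate.

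Age and sex appear later in the same section, in additional multivariable linear regressions. Their other main terms are ASIA grade or GCS score and concurrent medications, with further candidates from Table 3. The stated purpose is: "This ensures that observed associations between sodium channel fragment levels and outcomes such as spasticity are robust".

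Two other statements bear on this. Baseline data says that data were collected to "ensure comparability across the three participant groups". Strengths and limitations says: "Patient factors like demographics and comorbidities may affect fragment levels".

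**The concern.** The article names demographics as a possible influence on the biomarker and claims comparable groups, but describes nothing that would produce comparability for the controls. Tabulating baseline data shows an imbalance; it neither prevents nor corrects one. A common range of 57 years (75 − 18) leaves ample room for volunteers to differ from trauma patients in age or sex mix.

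The regression is the only place where age and sex are adjusted for, and as listed it fits patients. ASIA grade and GCS are severity measures for SCI and TBI, Table 1 gives no neurological assessment for controls, spasticity is not assessed in them, and Table 3 describes data collected from patients.

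At stake is how the difference between patients and controls is read. If demographics move fragment levels and the groups differ in them, part of a difference attributed to injury is not due to injury. The same applies to the baseline values that the control group is meant to supply.

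**Working it through.** **Reading the text.** Set side by side, the sections give: no matching rule; no covariate in the three-group test; an age and sex model whose listed terms include some that are undefined for controls and whose stated target is patient outcomes. The article gives no effect size, SD or power, so there is no figure of the plan to reproduce.

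**Inputs from the document.** Group sizes 10 controls, 20 SCI, 10 TBI; two-sided 5% level; ANOVA or Kruskal-Wallis.

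**Inputs assumed, because the document gives none.** Both patient groups differ from controls in mean age by g standard deviations; the correlation between marker and age within groups is r; injury has no effect.

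**Model.** Marker = r × age + √(1 − r²) × noise, with age and noise standard normal and g added to age in patients. The spurious patient-control difference is g × r, in SD units: 0.5 × 0.2 = 0.10 at the low end and 1.0 × 0.5 = 0.50 at the high end.

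**False-positive rates of the three-group test** (20,000 simulated trials per row; simulation error about 0.15–0.3 percentage points):

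| Age gap (SD) | r | Spurious difference (SD) | Kruskal-Wallis | ANOVA | Linear model adjusted for age |
|---|---|---|---|---|---|
| 0.5 | 0.2 | 0.10 | 5.0% | 5.4% | 4.9% |
| 0.5 | 0.3 | 0.15 | 5.9% | 6.2% | 4.9% |
| 0.5 | 0.4 | 0.20 | 6.4% | 6.8% | 4.8% |
| 0.5 | 0.5 | 0.25 | 7.9% | 8.6% | 4.9% |
| 1.0 | 0.2 | 0.20 | 6.6% | 7.4% | 5.1% |
| 1.0 | 0.3 | 0.30 | 9.4% | 10.2% | 5.0% |
| 1.0 | 0.4 | 0.40 | 13.3% | 14.3% | 5.1% |
| 1.0 | 0.5 | 0.50 | 18.1% | 19.6% | 5.1% |

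With no age gap, Kruskal-Wallis rejects in 4.6–4.8% and ANOVA in 5.0%, so the excess comes from the gap.

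**Sex.** Assume 80% men among patients, 50% among controls, and a sex effect of 0.5 or 1.0 SD. The spurious difference is (0.80 − 0.50) × 0.5 = 0.15 SD or (0.80 − 0.50) × 1.0 = 0.30 SD. Unadjusted ANOVA then rejects in 7.0% or 8.7% of trials (4,000 runs); adjusted for sex, in 5.2% or 4.7%.

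**Scale.** The standardized difference detectable with 80% power is (1.96 + 0.84) × √(1/20 + 1/10) ≈ 1.09 for SCI against controls and (1.96 + 0.84) × √(1/10 + 1/10) ≈ 1.25 for TBI against controls. A spurious 0.50 SD is just under half of the first (0.50 / 1.09 = 0.46).

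**The case against.** The strongest reply is that the article does not exclude controls from the regression. It lists age and sex as confounders and gives spasticity only as an example of an outcome. A reader might infer that the adjustment definitely omits controls; the text does not say so. How covariates enter for controls is a detail that an analysis plan could settle. This stands, and so the point is that coverage is unclear. It does not remove the point: the three-group test itself is fixed without covariates, and the listed regression cannot be fitted to controls as it is written.

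A reader might also infer that diagnostic cut-offs are biased. They are not touched: the planned ROC curves separate SCI from TBI or predict spasticity onset, and neither uses controls.

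The authors disclose the demographic issue and say that larger studies are needed for normative ranges; the study is called a pilot, and a baseline table is planned. The same medical exclusions apply to all three groups, which removes part of any comorbidity imbalance. All of this is fair, but none of it deals with age or sex.

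Finally, it is tempting to quote the pairwise SCI-control test alone at a 1-SD gap, where Mann-Whitney rejects in 7.1% to 20.8% of trials for r = 0.2 to 0.5. The plan runs pairwise tests after the overall test. If Kruskal-Wallis must first be significant, the range falls to 3.8–13.8%, and at a 0.5-SD gap to 2.3–4.9%. The reference for these gated figures is about 2.3% (the rate with no age gap), not 5%. Under mild assumptions the distortion is small.

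**Conclusion.** The point holds for the group-level contrast between patients and healthy controls. No age or sex matching is stated, the main test is unadjusted, and the regression does not clearly extend to this contrast, while the article itself grants that demographics may matter and claims comparability.

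The size is unknown. For assumed age gaps of 0.5–1 SD and marker-age correlations of 0.2–0.5, the overall Kruskal-Wallis error rate is about 5–18% (ANOVA about 5–20%) against a nominal 5%. These figures illustrate sensitivity; they do not estimate this trial's error rate, since the document supports no particular gap, direction or correlation. If fragment levels barely depend on age or sex, the effect is negligible. The change is worth making because it is cheap and because matching is possible only before the controls are sampled.

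**What to change.** 1. Prespecify, alongside the unadjusted test, one analysis of the patient-control contrast adjusted for age and sex only, with no ASIA, GCS or drug terms. State which participants enter each regression. With age linear and sex binary this uses two degrees of freedom: residual degrees of freedom fall from 40 − 3 = 37 to 40 − 5 = 35. Ten controls will not support many more terms.
2. Frequency-match the 10 controls to the enrolled patients by sex and broad age band, by filtering the existing registry. Keep the adjustment, since matching in broad bands leaves some imbalance.
3. Enrol controls in parallel with patients and assay them in the same batches. Leaving controls to the end would ease matching but could create a difference in storage time or batch between groups.
4. Reword the Baseline data statement so that the table describes comparability and is not said to ensure it.

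The cost is that controls cannot all be enrolled at the start, together with the two degrees of freedom. No extra participants or samples are needed. If controls have already been sampled, only items 1 and 4 and common assay batches remain available.

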#### Group 2: Spinal Cord Injury (SCI) patients.

SCI patients are prospectively recruited from the Intensive Care Unit or Neurosurgical Department at Hôpital Nord within 6 hours post-trauma. Upon admission, interventions for these patients begin with clinical and imaging assessments. A computed tomography (CT) scan is performed on admission to confirm vertebral fractures or spinal column instability. Magnetic resonance imaging (MRI) provides detailed characterization of the SCI, documenting patterns such as contusion, compression, hemorrhage, or edema. Injury severity is further classified using the AOSpine fracture classification [39] and BASIC scoring system [40,41].

Baseline neurological status is documented using the American Spinal Injury Association (ASIA) Impairment Scale, which evaluates the severity and level of the SCI [39,42]. Additional documentation includes respiratory and hemodynamic stability, renal clearance, liver function, and hemoglobin levels.

Blood sampling begins with a 4 mL venous sample collected within the 6 hours of trauma. Additional samples are collected during the acute phase on days 1, 3, 5, 7 and 14 to monitor early biomarker kinetics. Further samples are obtained at 3 months (M3) and 6 months (M6) post-trauma, offering insights into long-term biomarker dynamics. As part of the follow-up interventions, at M3 and M6, spasticity is assessed using the **Modified Ashworth Scale** (MAS, Table 2), alongside detailed evaluations of neurological recovery and residual deficits. These assessments are complemented by documentation of neurological recovery and residual deficits, enabling correlations between clinical outcomes and sodium channel fragment levels.

**Table 2 pone.0319635.t002:** Modified Ashworth scale for spasticity assessment [44].

Modified Ashworth score	Clinical findings
0	No increase in muscle tone
1	Slight increase in muscle tone, with a catch and release or minimal resistance at the end of the range of motion when an affected part(s) is moved in flexion or extension
1+	Slight increase in muscle tone, manifested as a catch, followed by minimal resistance through the remainder (less than half) of the range of motion
2	A marked increase in muscle tone throughout most of the range of motion, but the affected part(s) are still easily moved
3	Considerable increase in muscle tone, passive movement difficult
4	Affected part(s) rigid in flexion or extension

#### Group 3: Traumatic Brain Injury (TBI) patients.

Interventions for TBI patients are tailored to intracranial trauma and are similar in structure to those for SCI patients, with modifications to address brain injury specifics. A whole-body CT scan is performed upon admission to confirm intracranial hemorrhage and exclude SCI, ensuring group specificity. Neurological status is assessed using the Glasgow Coma Scale (GCS) to document the severity of brain injury [43]. Trauma-related data, including respiratory and hemodynamic stability, renal clearance, liver function, and hemoglobin levels, are recorded. Blood sampling begins with a 4 mL venous sample collected within the 6 hours of trauma during the routine biological workup. Additional samples are obtained during the acute phase at Days 1, 3, 5, 7 and 14 to capture early biomarker dynamics. Further samples are collected during late follow-up visits at M3 and M6 to evaluate the longer-term biomarker behavior. General neurological assessments are performed at M3 and M6 to evaluate recovery. These outcomes are correlated with sodium channel fragment levels to explore potential biomarker-based prognostication.

For SCI and TBI patients (Groups 2 and 3), detailed records of all medical treatments administered during hospitalization will be maintained. This includes, but is not limited to: anticoagulation therapy, antibiotic regimens, anti-spastic medications, and pain management protocols. This documentation allows for the evaluation of potential confounding factors and ensures that biomarker changes can be interpreted in the context of treatment.

### Outcomes

**The primary outcome** of the study is the detection and quantification of sodium channel fragments in blood samples. These fragments are quantified using a semi-automated Western blot technique employing the commercial Pan-Nav antibody, which is validated for its high sensitivity in detecting α-subunit cleavage products generated by calpain-mediated proteolysis. Sodium channel fragment levels are compared across SCI, TBI and healthy participants to identify injury-specific biomarker signatures. These data aim to provide valuable insights into the molecular mechanisms underlying SCI and TBI.

The **secondary outcomes** include:

1**Temporal Dynamics of Sodium Channel Fragments:** The temporal kinetics of sodium channel fragments are analyzed to characterize their dynamic expression and persistence during the acute and chronic phases of injury. Longitudinal changes in fragment levels are assessed from the baseline (acute phase) through follow-up visits at 3 months (M3) and 6 months (M6). These data are related with key clinical and functional outcomes to evaluate the role of sodium channel fragments as potential prognostic biomarkers. For SCI patients, changes in neurological function are monitored using the American Spinal Injury Association (ASIA) Impairment Scale, which provides detailed assessments of sensory and motor function recovery. For TBI patients, functional recovery is evaluated using the Glasgow Outcome Scale (GOS) and the more granular Glasgow Outcome Scale-Extended (GOSE), which capture subtle variations in recovery trajectories. For both groups, quality of life is assessed using the Short Form Health Survey (SF-36), a comprehensive tool that evaluates health-related quality of life across physical, mental, and social dimensions. These correlations aim to establish the predictive value of sodium channel fragment levels for neurological recovery, functional outcomes, and overall quality of life, providing a deeper understanding of the molecular mechanisms underlying injury progression and recovery.2**Spasticity and Biomarker Levels in SCI Patients:** The relationship between sodium channel fragment levels and spasticity is specifically investigated in SCI patients. Spasticity is assessed during follow-up visits at M3 and M6 using the Modified Ashworth Scale (MAS), a widely used tool for grading muscle tone. The relationship between MAS scores and fragment levels is evaluated using correlation analyses. This correlation is expected to provide evidence of the prognostic utility of sodium channel fragments in predicting the onset and severity of spasticity. These analyses aim to establish the prognostic utility of sodium channel fragments in predicting the onset, progression, and severity of spasticity, providing a molecular link between injury mechanisms and clinical outcomes. Such insights may inform personalized therapeutic strategies for managing spasticity in SCI patients.3**Injury Severity and Biomarker Associations:** The study investigates the association between sodium channel fragment levels and injury severity in both SCI and TBI patients. For SCI patients, neurological severity is assessed using the ASIA Impairment Scale, which evaluates the level and completeness of spinal cord injury through sensory and motor function tests. For TBI patients, the severity of brain injury is determined using the GCS, which provides a standardized assessment of consciousness based on eye, verbal, and motor responses. By correlating sodium channel fragment levels with these established severity metrics, the study aims to elucidate the relationship between molecular biomarkers and clinical injury severity, enhancing the understanding of the pathophysiology of CNS trauma and informing future diagnostic approaches.
